#### Analyses of Longer Term Objectives

Decreased premature mortality is the long-term goal of the development of the WittyFit software. Considering this censored data, estimation will be performed as described previously using the Kaplan-Meier approach. Comparison with historical cohorts and previous research will be included in the estimates of 95% confidence intervals. WittyFit’s effect will be also studied using log-ranked comparisons and a Cox proportional hazards model. Multivariate models will be used according to univariate results and clinical and epidemiological relevance.

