**Methods:**

This is an exploratory interventional cohort study in an ecological situation. Three groups of participants will be purposefully sampled: employees, middle managers, and executive managers. Four levels of engagement are planned for employees: commencing with baseline health profiling from validated questionnaires; individualized feedback based on evidence-based medicine; support for behavioral change; and formal evaluation of changes in knowledge, practices, and health outcomes over time. Middle managers will also receive anonymous feedback on problems encountered by employees, and executive top managers will have indicators by division, location, department, age, seniority, gender and occupational position. Managers will be able to introduce specific initiatives in the workplace. WittyFit is based on two databases: behavioral data (WittyFit) and medical data (WittyFit Research). Statistical analyses will incorporate morbidity and well-being data. When a worker leaves a workplace, the company documents one of three major explanations: retirement, relocation to another company, or premature death. Therefore, WittyFit will have the ability to include mortality as an outcome. WittyFit will evolve with the waves of connected objects further increasing its data accuracy. Ethical approval was obtained from the ethics committee of the University Hospital of Clermont-Ferrand, France.

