### Participants

All workers agreeing to participate in the WittyFit study will be included from any companies willing to permit their employees to be invited to participate. The WittyFit concept follows an epidemiological design without sample size limitation. Like the Nutrinet-Santé study [57-63], the WittyFit study is never expected to end. Recruitment will commence in January 2016, and data collection will be ongoing due to the prolonged longevity of the project. Duration of participation per individual is unlimited. A staggered strategy will be to target a sample size of 200 workers from Voyages-SNCF.com within the first 6 months in order to improve and evolve the WittyFit software. WittyFit will then extend to other companies in the following year.

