### Objectives

The shorter term objectives will be to demonstrate that WittyFit improves parameters of well-being and morbidity based on three major health-related behavioral categories. The mid-term objectives will be to demonstrate that WittyFit improves economic data of the companies such as productivity and benefits. The primary long-term objective will be to demonstrate that WittyFit will contribute to decrease premature mortality.

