### Statistical Considerations

#### Sample Size Calculations

Using only Internet or computer interventions for behavior change outcomes improving eating disorders and nutrition [76], weight and cardiorespiratory fitness [77], or mood [78] and stress related to the workplace and performance and productivity [79], the sample size estimation was performed according to Cohen’s recommendations with the following defined effect size (ES) bounds: small (ES 0.2), medium (ES 0.5), and large (ES 0.8, “grossly perceptible and therefore large”) [80]. Considering an effect size of 0.33, a 2-tailed type I error fixed at a=0.001 to take into account multiple comparisons, and a moderate loss to follow-up rate, N=1000 participants will allow us to highlight (1) such ES for a statistical power greater than 95% for paired comparisons (n=225 with a correlation coefficient of .5) and (2) such ES for a statistical power greater than 80% for intergroup comparisons (n=311 by group).

For life expectancy, 100,000 workers followed over 5 years would provide a sufficient and relevant sample size to achieve the long-term objectives measured by this study. Purposive sampling will be conducted to best draw comparisons with previous research [81] studying leisure time spent sitting in relation to total mortality in a prospective cohort of US adults [9] and to further elucidate job strain among blue-collar and white-collar employees. Job strain has previously been associated with total mortality in a 28-year cohort study [82]. To address the objective of reducing premature mortality, statistical power estimation was based on a hazard ratio used for censored data (hazard ratio of 1.25 and 2) and in accordance with previously described data. This hazard ratio estimate was proposed to support a type I error of 5% (2-sided) with statistical power at 95% (see Figure 7). However, the study will be unlimited within the long-term aspects of its epidemiological design.

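### The mortality objective is read partly against historical cohorts, and the one stated route to comparability, purposive sampling, is in tension with open enrolment, so age or calendar-time differences could pass for a WittyFit effect

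*Protocol article*

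**What the plan says.** The Objectives section sets the aim: "The primary long-term objective will be to demonstrate that WittyFit will contribute to decrease premature mortality".

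Analyses of Longer Term Objectives estimates mortality by Kaplan-Meier and then says: "Comparison with historical cohorts and previous research will be included in the estimates of 95% confidence intervals". It continues: "WittyFit’s effect will be also studied using log-ranked comparisons and a Cox proportional hazards model", and "Multivariate models will be used according to univariate results and clinical and epidemiological relevance". The groups that the log-rank test and Cox model would compare are not named, and no concurrent unexposed group appears anywhere in the article.

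On comparability, Sample Size Calculations says: "Purposive sampling will be conducted to best draw comparisons with previous research". The research meant is a study of sitting time and total mortality "in a prospective cohort of US adults". A 28-year job-strain cohort is cited in the same paragraph. The abstract also speaks of purposive selection, by level in the company: "Three groups of participants will be purposefully sampled: employees, middle managers, and executive managers".

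The enrolment rule in Participants reads differently: "All workers agreeing to participate in the WittyFit study will be included from any companies willing to permit their employees to be invited to participate". That section also says the design has no sample size limitation.

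**The concern.** All-cause mortality depends strongly on age, sex, country and calendar period. When the reference is an outside cohort, any difference in these is mixed with the effect of the intervention. The article's stated answer is to sample so that comparison is possible, but a rule that accepts every volunteer from every willing company does not let workers be selected to resemble a reference cohort.

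At stake is the study's ultimate claim. If WittyFit had no effect on mortality, a cohort slightly younger or later in calendar time than its reference would still show fewer deaths. With 100,000 workers that deficit would look precise. The problem would remain even if every death were captured.

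**Working it through.** **The plan's own figure.** The inputs in Sample Size Calculations are 100,000 workers, 5 years, hazard ratios of 1.25 and 2, two-sided 5% error and 95% power. Schoenfeld's formula for two equal groups gives deaths = 4 × (1.960 + 1.645)² / (ln HR)²:
- HR 1.25: 4 × 12.995 / 0.0498 = 1,044 deaths, about 2.1 per 1,000 person-years over 100,000 × 5 = 500,000 person-years.
- HR 2: 4 × 12.995 / 0.4805 = 109 deaths.

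The text gives no death rate or group split, and Figure 7 is not shown, so the 100,000 can be neither confirmed nor refuted. The ratio of 1.25 (inverted, 1/1.25 = 0.80) serves below only as a yardstick for bias. The article does not say that it is a WittyFit-versus-historical contrast.

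**Age gap that alone produces the yardstick.** Assumption, not in the document: mortality rises by g per year of age. Years needed = ln(1.25) / ln(1 + g).
- g = 8%: 0.2231 / 0.0770 = 2.9 years.
- g = 10%: 0.2231 / 0.0953 = 2.3 years.
- Widening g to 7-11% gives 3.3 to 2.1 years.
- For a ratio of 2, ln(2) / ln(1 + g) gives 9.0 years at 8% and 7.3 years at 10%.

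A WittyFit cohort that is younger than its reference moves the ratio towards benefit. An older one hides benefit.

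**Calendar gap that alone produces 0.80.** Assumption, not in the document: mortality falls by d per calendar year. Years needed = ln(0.80) / ln(1 − d).
- d = 1%: 22.2 years.
- d = 1.5%: 14.8 years.
- d = 2%: 11.0 years.

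For scale, suppose the 28-year cohort were used as a reference. If its follow-up ended no later than January 2016, its midpoint lies at least 28/2 + 5/2 = 16.5 years before the midpoint of a 2016-2021 follow-up. The ratio from period alone would then be 0.99^16.5 = 0.85, 0.985^16.5 = 0.78 or 0.98^16.5 = 0.72.

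**What sample size does to a biased ratio.** Assumption: 1-3 deaths per 1,000 person-years, so 500-1,500 expected deaths in 500,000 person-years. Suppose WittyFit has no effect and mismatch gives a ratio of 0.80, so 400-1,200 deaths are observed. Treating the reference as fixed, the 95% interval is 0.80 × exp(±1.96/√observed):
- 400 deaths: 0.73 to 0.88.
- 1,200 deaths: 0.76 to 0.85.

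Both intervals exclude 1, and the larger count only tightens the interval around the wrong value.

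**Which stated measures could remove the mismatch.**
- Purposive sampling: workers cannot be selected under the Participants rule. Companies or sectors could be, but that leaves country and calendar period unchanged.
- Multivariate Cox models: these could adjust for differences from an outside cohort only if its individual records were pooled with WittyFit's. Pooling is not stated.
- Age and gender fixed effects in Analyses of Shorter Term Objectives: these belong to the repeated-measures models of well-being and morbidity.
- Sector numbers in Quality Control Measures: these are offered for generalizability, not for matching to a reference cohort.

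**The case against.** Several stronger readings are tempting, and the article does not support them.

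- A reader might infer that the enrolment rule makes purposive sampling impossible. It does not: how companies are approached is left open, the roll-out is staggered, and sectors are to be filled deliberately. There is a tension to reconcile, not an impossibility.
- A reader might infer that sampling is the only protection of any kind. The multivariate models are also there. The article never says that the historical cohorts would be available only as published results, so adjustment from pooled records cannot be excluded. It is simply not stated.
- A reader might infer a direct Kaplan-Meier comparison with the US and 28-year cohorts. Kaplan-Meier is named for estimation, and no method is given for the historical comparison. The longer-term section does not name its historical cohorts. The US cohort is tied to comparison in the sample-size text, in connection with an association between sitting and mortality. The 28-year cohort as a comparator is an inference.
- A reader might convert the bias into a false-positive rate for the study. No one-sample test against an error-free reference is planned, and the death rate and the bias would both be assumed.
- A reader might count the absence of standardisation as an omission. This is a condensed article whose original protocol is an appendix not shown, so silence on that detail is no finding.

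It is also fair that the study calls itself exploratory, and that national rates bring their own bias because workers and volunteers are healthier than the population. What survives is the stated choice of comparator for the primary long-term objective and the conflict between two stated rules. Neither depends on detail that the appendix might supply.

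**Conclusion.** The point holds in limited form and is a cheap improvement rather than a fatal flaw. Comparison with historical cohorts is a stated part of the mortality assessment, no concurrent unexposed group is named, and the one device stated for comparability with previous research fits poorly with the enrolment rule.

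An age gap of about 2-3 years, or a calendar gap of about 11-22 years, would be enough to imitate the smaller planned hazard ratio. This rests on assumed gradients of 8-10% per year of age and 1-2% per calendar year. The article gives no death rates, no age structure and no dates for any comparator, so it cannot be said that such gaps exist, only that gaps of this size would matter. The larger planned ratio of 2 is not within easy reach: it would take an age gap of roughly 7-9 years under the same gradients, or several differences acting together.

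**What to change.** - For the external mortality comparison, count person-years by attained age, sex and calendar year while each worker is under observation. Apply national rates specific to age, sex and calendar year to obtain expected deaths, and report the standardised mortality ratio with its 95% confidence interval.
- Label comparisons with the historical cohorts, and the standardised ratio itself, as descriptive and not as evidence that WittyFit reduces mortality. Standardisation deals with age, sex, country and period, but healthy-worker and volunteer selection remain and push the ratio in the same direction as a benefit. Say so beside the result.
- Reconcile the purposive-sampling sentence in Sample Size Calculations with the rule in Participants. Either state that the purposive choice applies to companies or sectors and what it is meant to achieve, or remove the claim that it serves comparison with previous research.

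The cost is a little more analysis work with published mortality tables. Age and gender are already among the variables the article uses, so no new data collection is needed. The real price is a weaker stated conclusion on mortality, which is what this comparison can support.

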#### Analyses of Shorter Term Objectives

To study WittyFit’s effect on morbidity and well-being, analyses will include comparisons with historical cohorts and literature and within the paired data from individual participants as they generate their own basis for comparison. To study longitudinal evolution of parameters associated to morbidity and well-being, models for repeated measures will be performed using a random-effects model (linear or generalized linear) along with fixed effects for descriptive data (eg, gender, age, body mass index, type of contract [full-time, part-time], professional roles [unskilled, skilled, mid-level workers, and senior executives] and occupational sector [commercial activities and service, health and social services, manufacturing/blue collar industries, finance officers]) taking into account within and between participant variability and company variability. All effect sizes will be presented with 95% confidence intervals.

When appropriate, comparisons between subgroups described above will be performed. Typical statistical tests will be applied: chi-square or Fisher exact tests for comparisons between groups from categorical parameters and analysis of variance or Kruskal-Wallis test for quantitative variables. The Shapiro-Wilk test will be used to assess normality, and the Fisher-Snedecor test to assess homoscedasticity. For censored data, the time-to-event curves will be estimated with the use of the Kaplan-Meier method. Comparisons will be performed by log-rank test. Then, Cox proportional-hazards regression models will be considered to study the prognostic factors in a multivariate situation by backward and forward stepwise modeling on the factors considered significant in univariate analysis and in accordance with parameters of clinical relevance [83,84]. The proportional-hazard hypothesis will be verified using Schoenfeld’s test and plotting residuals. The interactions between possible predictive factors will also be tested. Results will be expressed as hazard ratios and 95% confidence intervals. Considering repeated correlated censored data, marginal models may be preferred.

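### The mortality analysis does not carry forward the company effect used for the shorter-term outcomes; if mortality differs by company, the historical-comparison interval and tests of exposures that vary by company are too optimistic

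*Protocol article*

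**What the plan says.** The Participants section enrols workers through their employers: they are "included from any companies willing to permit their employees to be invited to participate". The Manager Feedback section lets managers act on results in their own workplace, so part of the intervention is delivered at company or department level. The section on economic outcomes has each company report why a worker left, death included.

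For the shorter-term outcomes, Analyses of Shorter Term Objectives specifies a linear or generalized linear random-effects model "taking into account within and between participant variability and company variability". The survival methods in the same section have no such term. They end with an optional sentence: "Considering repeated correlated censored data, marginal models may be preferred".

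For mortality, Analyses of Longer Term Objectives plans Kaplan-Meier estimation and adds: "Comparison with historical cohorts and previous research will be included in the estimates of 95% confidence intervals". For testing the software, the section then says that its "effect will be also studied using log-ranked comparisons and a Cox proportional hazards model". Company is not mentioned, and the groups to be compared are not defined. Sample Size Calculations gives 100,000 workers over 5 years, a "hazard ratio of 1.25 and 2" and a "type I error of 5% (2-sided) with statistical power at 95"%.

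**The concern.** The article recognises that workers in one company resemble each other and builds this into one analysis, but not into the analysis of its primary long-term objective. The Kaplan-Meier interval, log-rank test and Cox model in their ordinary form treat workers as independent. Companies plausibly differ in sector, occupational mix and completeness of death reporting, and their managers choose different initiatives.

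Variation left out of the standard error makes the result look more precise than it is. A difference from a historical cohort, or between companies with and without an initiative, could then be credited to WittyFit when it only reflects which companies joined. A large number of workers does not cure this, because the excess variance grows with the number of deaths per company.

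**Working it through.** **The plan's own figure.** Figure 7 is not shown, and the text gives neither baseline mortality nor the share of workers exposed, so the 100,000 cannot be reproduced. With two equal groups, two-sided 5% and 95% power, the Schoenfeld formula for a hazard ratio of 1.25 requires 4 × (1.960 + 1.645)² / (ln 1.25)² = 51.98 / 0.0498 = 1,044 deaths. That is 1.04% of 100,000 workers. For a hazard ratio of 2 it is 109 deaths. A five-year mortality of about 1% is therefore a reasonable working assumption, but it is not a figure from the article.

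**Assumptions.** 100,000 workers; 1% five-year mortality; 500, 100 or 20 equal companies; between-company coefficient of variation (CV) of the death rate 0.1 to 0.3. None of the company inputs is in the article.

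**Formulas.** With D expected deaths per company, the design effect is DE = 1 + D × CV². A nominal 5% test that ignores company has a true type I error of 2 × [1 − Φ(1.96/√DE)] when exposure differs wholly between companies. The correct interval is √DE times as wide as the ordinary one.

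Example with 100 companies of 1,000 (D = 10) and CV 0.2: DE = 1 + 10 × 0.04 = 1.4; 1.96/√1.4 = 1.66; type I error 9.8%; correct interval 1.18 times as wide.

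| Companies × workers (D) | CV 0.1 | CV 0.2 | CV 0.3 |
|---|---|---|---|
| 500 × 200 (2) | 5.2% | 5.9% | 7.1% |
| 100 × 1,000 (10) | 6.2% | 9.8% | 15.5% |
| 20 × 5,000 (50) | 11.0% | 25.8% | 40.3% |

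Simulation with gamma-distributed company rates agrees: 6.2%, 9.6% and 15.9% for 100 companies; 10.8%, 25.7% and 40.2% for 20.

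**Historical comparison.** Here exposure need not vary between companies; it is enough that mortality does. With 100 companies of 1,000, simulated coverage of the ordinary 95% interval for the wider population of companies is 92.5%, 88.8% and 83.6% at between-company variances of 0.02, 0.05 and 0.1 (CV about 0.14, 0.22 and 0.32).

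**Where exposure varies.** With 100 companies of 1,000 and variances of 0.02 to 0.2 (CV about 0.14 to 0.45), the simulated type I error of the ordinary test is:

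- wholly between companies: 7.1% to 25.5%
- uptake varying from 20% to 80% across companies: 5.0% to 7.8%
- equal uptake in every company: 4.9% to 5.0%

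**Power, if the contrast were between companies.** Φ(3.605/√DE − 1.96) turns 95% into 93%, 86% and 74% for D = 10 and CV 0.1, 0.2 and 0.3. The article does not tie its 95% to such a contrast.

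**The case against.** A reader might infer that the mortality analysis certainly has intervals that are too narrow and a false-positive rate above 5%. The article does not support that, for four reasons.

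- **Silence.** The section names methods, not variance estimators. A Cox model with clustered standard errors is still a Cox model, and the full protocol, cited as an appendix, is not shown. This stands as a caution. But the article does name company in its other model, so the omission is a difference within the article's own stated methods.
- **Undefined contrast.** The stated hypothesis concerns effective use of the software, which can vary within a company. With similar uptake everywhere, log-rank and Cox tests stay near 5%. This stands, and limits the point on those tests to exposures that vary between companies. It does not touch the historical comparison.
- **Target of inference.** For mortality in the enrolled companies alone, the ordinary interval has its nominal coverage. This also stands. Yet the article hopes to generalise to occupational sectors and sets its estimate against outside cohorts, which calls for inference beyond those companies.
- **Marginal models and covariates.** Marginal models are a standard way to handle clustered survival data, and adjusting for sector and occupation could remove part of the variation. But the sentence on marginal models is optional, is worded for repeated data and does not name company. Each worker dies only once. Covariates cannot remove differences that they do not measure, such as completeness of death reporting.

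**Conclusion.** The point holds in conditional form. The mortality section leaves out the company effect that the article uses for its shorter-term outcomes. The consequence needs between-company variation in mortality or death reporting and, for the log-rank and Cox tests, an exposure that varies between companies as well. The comparison with historical cohorts is the most exposed part, because it needs only the first condition.

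The size cannot be fixed from the article. It is negligible with many small companies or little variation, about 6% to 16% type I error in the middle scenario, and much larger if a few big companies supply most workers. The power losses shown apply only if the powered contrast is between companies, which the article does not say. It is worth correcting before mortality data are analysed.

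**What to change.** In Analyses of Longer Term Objectives:

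1. State the mortality contrast: users versus non-users within companies, companies with versus without an initiative, or the cohort against historical data.
2. Fit the Cox model with company-clustered robust variance or a company shared frailty. For exposures that vary between companies, use that test in place of the ordinary log-rank P value.
3. Obtain the interval set against historical cohorts by company-level bootstrap or robust variance.
4. If companies are few, add a small-sample correction, for example a t reference or a company-level test. With 20 companies, a robust test with a normal reference still rejected about 7% of the time under the null in simulation, while a company-level t test held 4.6% to 5.2%.

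In Sample Size Calculations, note that the 95% power makes no stated allowance for between-company variation. If the contrast is between companies, show power over a range of CV such as 0.1 to 0.3.

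The cost is a few sentences, wider intervals and possibly a less favourable stated power. Employers already supply the data by company, so no extra workers or data are needed.

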**Objective:**

The shorter term feasibility objective is to demonstrate that effective use of WittyFit will increase well-being and improve health-related behaviors. The mid-term objective is to demonstrate that WittyFit improves economic data of the companies such as productivity and benefits. The ultimate objective is to increase life expectancy of workers.

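### The log-rank and Cox tests of WittyFit's effect on premature mortality have no unexposed comparison, because every participant in the cohort receives WittyFit

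*Protocol article*

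**What the plan says.** The Objectives section sets the primary long-term aim: to "demonstrate that WittyFit will contribute to decrease premature mortality". Analyses of Longer Term Objectives starts from Kaplan-Meier estimation and adds "Comparison with historical cohorts and previous research will be included in the estimates of 95% confidence intervals". It then says that WittyFit's "effect will be also studied using log-ranked comparisons and a Cox proportional hazards model". It names no groups, exposure variable or time origin for these tests.

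The rest of the article fixes who is observed:

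- Abstract, Methods: "This is an exploratory interventional cohort study in an ecological situation".
- Participants: "All workers agreeing to participate in the WittyFit study will be included". Enrolment starts in one company and extends to others in the following year.
- Economic Outcomes and Outcomes Provided by Employers: when a participant leaves the database, the company gives the reason, and death is one of the three. No reporting of deaths is described for anyone else.
- Analyses of Shorter Term Objectives: the comparators are historical cohorts, the literature, and comparison "within the paired data from individual participants as they generate their own basis for comparison".
- Abstract, Objective: the short-term claim is that "effective use of WittyFit will increase well-being and improve health-related behaviors". The Introduction repeats this as the short-term hypothesis. The wording about effective use appears in neither the mortality objective nor the mortality analysis.

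**The concern.** A two-sample log-rank test, or a Cox model with a term for WittyFit, compares mortality in people or person-time with WittyFit against mortality without it. This cohort has no person-time without it. The named tests therefore cannot deliver the quantity that the primary long-term objective asks for. This is a mismatch between analysis and design, and more than an omitted detail.

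There is a second, conditional risk. An analyst who has to run these tests on this cohort may turn to level of use as the contrast. Use builds up after enrolment, through scales prompted every 15 days and questionnaires every 6 months. A worker must survive to the point of qualifying as a user. If users and non-users are then compared from enrolment, all deaths before that point fall on the non-users, and an inert program looks protective.

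**Working it through.** **Step 1. Look for an unexposed comparison.**

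- *Concurrent controls:* none. Every consenting worker is included, in one interventional cohort.
- *Non-participants, or workers in companies that have not yet joined:* no death reporting is described for them, so the staggered roll-out supplies no documented unexposed person-time.
- *Own control:* paired data serve for repeated scores, but not for death.
- *Historical cohorts:* these are named, but in a separate sentence about the estimates and confidence intervals. The word *also* in the log-rank and Cox sentence reads as an addition to that comparison.

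**Step 2. See whether the power statement defines the contrast.** Sample Size Calculations gives 100,000 workers over 5 years, hazard ratios of 1.25 and 2, two-sided alpha 5% and power 95%. The 100,000 cannot be reproduced, because the readable text gives no death rate or group split and Figure 7 is not shown. Schoenfeld's formula with an assumed 1:1 split gives:

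- HR 1.25: (1.960 + 1.645)² / [0.25 × (ln 1.25)²] = 1044 deaths
- HR 2: (1.960 + 1.645)² / [0.25 × (ln 2)²] = 109 deaths

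At an assumed 2 deaths per 1000 person-years, 100,000 × (1 − e^(−0.01)) ≈ 995 deaths, which gives 94% power at HR 1.25. The total is plausible at that rate, but the calculation needs two groups. The mortality research cited there concerns sitting time and job strain, so no WittyFit contrast is defined here either.

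**Step 3. Size the bias if use were the contrast.** Assumptions, none from the article except the 5 years: no true effect; deaths rare at constant rate λ; follow-up T; a share p of those alive at threshold L count as users; groups fixed from enrolment.

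- User rate: λ(T − L)/T
- Non-user rate: λ[L + (1 − p)(T − L)] / [(1 − p)T]
- Spurious ratio: (1 − p)(T − L) / [L + (1 − p)(T − L)]

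The death rate cancels. With T = 5 years:

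| Users p | L = 0.5 y | L = 1 y |
|---|---|---|
| 30% | 3.15/3.65 = 0.86 | 2.8/3.8 = 0.74 |
| 50% | 2.25/2.75 = 0.82 | 2.0/3.0 = 0.67 |
| 70% | 1.35/1.85 = 0.73 | 1.2/2.2 = 0.55 |

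With L = 0.5 and p = 50%, longer follow-up weakens the bias: 4.75/5.25 = 0.90 at 10 years and 9.75/10.25 = 0.95 at 20 years.

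**Step 4. Check the remedy for the time element.** A null simulation (4,000,000 workers, 2 deaths per 1000 person-years, 5 years, half reaching the threshold) gives 0.82 at 6 months and 0.66 at 12 months with fixed groups, which agrees with the formula. Across thresholds of 0.5, 1 and 2 years and one spread evenly over the 5 years, time-dependent coding gives 0.98-1.02. A landmark at each of the three fixed thresholds gives 1.00-1.02.

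**The case against.** The strongest case against has four parts.

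**Immortal-time bias is not in the document.** A reader might infer that the protocol commits to a use contrast, and so that the analysis as written would show benefit from an inert program. The text does not support that. No section groups participants by use for mortality, and the phrase about effective use belongs to the short-term aim. Other internal contrasts are conceivable: baseline job strain or sitting time, manager initiatives, company entry date. This part stands, so the bias is a conditional warning.

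**The historical comparison may be the intended contrast.** The article lists historical cohorts separately from the literature, so individual records are not ruled out, and a one-sample log-rank test can set one cohort against reference mortality. This stands in part. Such a test would be legitimate if stated, but it is an external comparison of the kind proposed below, and the article does not tie its log-rank or Cox tests to one.

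**The bias need not exceed the planned effect.** This is correct. Inverted, the planned hazard ratios are 0.80 and 0.50. At 6 months the spurious ratio reaches 0.80 only when 0.9(1 − p) ≤ 0.4, that is p of about 56% or more. At 12 months it passes 0.80 throughout the table, but never reaches 0.50. Reading 1.25 as WittyFit's own planned effect is itself an inference. The study is also meant to continue without limit, which shrinks the bias.

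**Time handling belongs in an analysis plan.** This is fair for landmarks, lags and time origin, and their absence from a condensed article is no fault. It does not answer the main point. The article itself fixes both the single exposed cohort and the named tests, and the two do not fit.

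**Conclusion.** The point holds in this form: the log-rank and Cox tests of WittyFit's effect on premature mortality have no unexposed comparison in the cohort described, so they cannot estimate that effect. This rests on the text alone and affects the primary long-term objective.

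Immortal-time bias follows only if level of use becomes the exposure and is treated as fixed from enrolment. Under the assumptions in the working, the spurious ratio is then about 0.73-0.86 (6-month threshold) or 0.55-0.74 (12-month threshold). Correct time handling removes this component. It does not remove self-selection of healthier workers into heavier use.

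**What to change.** In Analyses of Longer Term Objectives:

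1. Base the comparison with no WittyFit on a standardised mortality ratio, by age, sex and calendar year, against external rates, instead of an internal log-rank test. State with it that people in work, and volunteers among them, may have lower mortality than the reference population whatever the program does.
2. Restrict internal log-rank and Cox analyses to exposures named in the text.
3. If one of these is use of WittyFit, enter it as a time-dependent covariate, or start risk time at a landmark. Adjust for baseline health and report an association with use, not an effect of WittyFit.

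The cost is analysis wording, plus obtaining suitable reference rates. Early deaths drop out of a landmark analysis, and the mortality conclusion becomes more modest than the objective now promises.
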